#### Concomitant Drug Use

For all patients, baseline information on other medications for CVD prescribed throughout follow-up will be captured from the pharmacy invoice (see ATC codes for drugs in Table 2).

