### Study Population

The study population includes individuals ≥18 years with an incident diagnosis of ACS during the study period 2006-2015, with at least two months of follow-up in the Information System for Research in Primary Care (SIDIAP) [12] after the index date. The next patients will be excluded: pregnant women on the index date; patients with a recorded diagnosis of ischaemic stroke in the six months prior to index date; patients living in a nursing home on the index date; and patients with Alzheimer’s disease or other dementias.

Case definition: patient with an incident diagnosis of ACS registered in CMBD-HA (dataset of diagnoses at hospital discharge) [13] of the Catalan Health Institute (ICS) within the period from 2006-2015. Index date definition: date of ACS episode.

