### Data Collection and Data Sources

Diagnoses for study inclusion and endpoints will be obtained from CMBD-HA, which contains diagnoses at hospital discharge from all ICS hospitals, coded with International Classification of Diseases, Nineth Revision (ICD-9) [14]; see Table 1.

The rest of the variables will be captured from SIDIAP, which contains anonymized clinical information of all 279 PHC centres managed by the ICS in Catalonia (North-East Spain), covering a population of more than 5.8 million patients (about 80% of the total of 7.5 million population in Catalonia). The information contained in SIDIAP is registered by PHC general practitioners (GP), nurses and administrative staff in ECAP (electronic health records in ICS): comprehensive sociodemographic information, health conditions registered as ICD10 codes [15], specialist referrals, clinical parameters, toxic habits, PHC laboratory test results, GPs prescriptions and their corresponding pharmacy invoice data registered as Anatomical, therapeutic, chemical classification system (ATC) codes [16], date of sickness leave due to any cause, and date of death. Several reports have shown that SIDIAP data is useful for epidemiological research [17-25]. SIDIAP is listed under the European Network of Centres for Pharmacoepidemiology and Pharmacovigilance (ENCePP) resources database [26].

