### Variables

#### Exposure Definition

Patients will be classified as “exposed” to the study drugs (antiplatelet agents, beta-blockers, ACEI or ARB, statins) if they are prescribed any of them after the episode of ACS (up to two months after the event). The dose prescribed in ECAP will be considered the daily dose used for the patient, and the number of tablets contained in each package will cover the same number of days (see drugs of study in Table 2).

**Table 1 table1:** International Classification of Diseases, Nineth Revision (ICD-9) codes for endpoints of study and procedures.

ICD-9 code	Description
411*	Unstable angina and other forms of acute coronary heart disease
410*	Acute myocardial infarction
433*, 434*, 435*, 436*, 437*	Ischaemic stroke
00.66, 36.03, 36.09, 39.50	Coronary angioplasty

**Table 2 table2:** Anatomical, therapeutic, chemical classification system (ATC) codes for drugs of interest.

ATC code		Description of therapeutic group

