#### Adherence Definition

To estimate medication adherence, we will calculate the PDC for all four study treatments during eight months of follow-up after the index date. The PDC calculation is based on the packages dispensed and days of supply for each package, considering that the number of tablets contained in one package covers the treatment necessary for 28 or 30 days, depending on the drug. The information will be obtained from the pharmacy invoice data. For the PDC calculation, the numerator is the number of packages dispensed (invoice register) during the first 8 months of follow-up, and the denominator is the period of 8 months, which is the period for the adherence measure. Based on the PDC, patient adherence to each study drug is usually classified into one of two categories using the standard threshold of 75% (≥75%: adherent, <75%: nonadherent) [6,9]. PDC=75% accounts for six packages (each one including one month of drug treatment) dispensed during eight months. We define adherent patients as those who have received at least six packages during the first eight months after the event. Finally, according to adherence to all four study drugs, patients will be classified as adherent if they get the refill for all study drugs: PDC antiplatelet ≥75% + PDC beta-blockers ≥75% + PDC ACEI/ARB ≥75% + PDC statin ≥75%.

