### Other Variables

All the following variables will be considered as potential confounders or effect modifiers in the association between adherence to the drug therapy and risk of the composite endpoint. They will be captured from SIDIAP database:

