#### Comorbidities and Clinical Parameters

They will be measured closest to the index date: type of cardiovascular event at index date (AMI and unstable angina and other forms of ACS captured from CMBD-HA), presence of coronary angioplasty implant after the event (data source CMBD-HA), cholesterol and other lipid parameters (low density lipoprotein-cholesterol, high density lipoprotein-cholesterol, total-cholesterol, and triglycerides), blood pressure measured (systolic and diastolic blood pressure), glycated hemoglobin, glomerular filtration rate, serum creatinine, specific comorbid conditions (see ICD-10 codes in Table 3), Charlson comorbidity index [28,29].

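### Use of the four study drug groups before the ACS is not a listed confounder, so pooling prior users with new starters may leave residual confounding of unknown size and direction in the adjusted HR

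*Protocol article*

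**What the plan says.** Under Study Population, the article includes "individuals ≥18 years with an incident diagnosis of ACS during the study period 2006-2015". Incident describes the ACS only. The exclusions are pregnancy, nursing-home residence, dementia and "patients with a recorded diagnosis of ischaemic stroke in the six months prior to index date". Earlier use of the study drugs is not an exclusion, and no washout is set.

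Under Exposure Definition, patients count as exposed "if they are prescribed any of them after the episode of ACS (up to two months after the event". Under Adherence Definition, "we will calculate the PDC for all four study treatments during eight months of follow-up after the index date". Both measures look forward from the index date only.

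Under Other Variables, the covariates are introduced with "All the following variables will be considered as potential confounders or effect modifiers". The list then covers patient characteristics, comorbidities and clinical parameters (including "specific comorbid conditions (see ICD-10 codes in Table 3), Charlson comorbidity index") and, under Concomitant Drug Use, the statement that "baseline information on other medications for CVD prescribed throughout follow-up will be captured from the pharmacy invoice". Table 2 separates the study drugs from the concomitant drugs.

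Under Data Collection and Data Sources, SIDIAP is said to hold "GPs prescriptions and their corresponding pharmacy invoice data".

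**The concern.** A patient with a first ACS may already be taking a statin, an antihypertensive or an antiplatelet. Such a patient can differ from a new starter in two ways that matter here: in how regularly packages are collected after the event, and in underlying cardiovascular risk. If both differences exist, prior use confounds the association between adherence and the composite endpoint.

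The Discussion names adjusted Cox models as the remedy for confounding, so the content of the covariate list matters. The listed diagnoses do not separate treated from untreated patients with the same diagnosis. Lipids and blood pressure are taken near the index date, so a well-controlled value on treatment and a naturally low value look alike unless prior treatment is in the model.

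At stake is the adjusted HR of the main objective. Secondary objective 2, on which baseline features go with adherence, would also be less informative without prior use of the same drugs.

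**Working it through.** **The plan's one related figure.** Sample Size gives 3415 cases in three years for all hospitals, an ICS share of about 30%, and ten study years: 3415 / 3 × 10 × 0.30 = 3415, against a stated figure of about 3400. It reproduces. It is a feasibility count and does not bear on confounding.

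**Is prior use covered anywhere?**
- Eligibility: no washout and no exclusion of prior users.
- Exposure and adherence: post-index records only.
- Patient characteristics, comorbidities and clinical parameters: no drug history.
- Concomitant Drug Use: restricted to other CVD drugs, and over follow-up. The sentence calls this baseline information, so the timing is unclear even for those drugs.
- Data sources: prescriptions and invoices are in SIDIAP, but no pre-index measure of the study drugs is planned from them.

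Prior users and new starters are therefore pooled, and no listed variable tells them apart.

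**How large could the effect be?** The article gives no prevalence of prior use and no risk ratio for it, so every input below is an assumption. For an unmeasured binary confounder (Bross bias factor):

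HR observed / HR true = (1 + p1(g − 1)) / (1 + p0(g − 1))

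Here p1 and p0 are the shares of prior users among adherent and nonadherent patients, and g is the HR of prior users against new starters that remains after the listed covariates. Prior use is simplified to one yes/no variable.

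| p1 / p0 | g = 0.7 | g = 1.0 | g = 1.3 | g = 2.0 |
|---|---|---|---|---|
| 0.4 / 0.4 | 1.00 | 1.00 | 1.00 | 1.00 |
| 0.5 / 0.4 | 0.97 | 1.00 | 1.03 | 1.07 |
| 0.6 / 0.4 | 0.93 | 1.00 | 1.05 | 1.14 |
| 0.7 / 0.4 | 0.90 | 1.00 | 1.08 | 1.21 |
| 0.5 / 0.3 | 0.93 | 1.00 | 1.06 | 1.15 |
| 0.6 / 0.3 | 0.90 | 1.00 | 1.08 | 1.23 |
| 0.7 / 0.3 | 0.87 | 1.00 | 1.11 | 1.31 |

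The extreme cells written out:
- (1 + 0.7 × (−0.3)) / (1 + 0.3 × (−0.3)) = 0.79 / 0.91 = 0.87
- (1 + 0.7 × 1.0) / (1 + 0.3 × 1.0) = 1.7 / 1.3 = 1.31

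**On the HR scale.** The Introduction cites a cohort with an HR of 0.72 for full adherence against nonadherence. That cohort studied statin and ACEI only and used other cut-offs, so it serves here only as a yardstick.
- Smallest contrast (0.5 / 0.4): 0.72 × 0.85 / 0.88 = 0.70 to 0.72 × 1.5 / 1.4 = 0.77.
- Largest contrast (0.7 / 0.3): 0.72 × 0.79 / 0.91 = 0.63 to 0.72 × 1.7 / 1.3 = 0.94.

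If prior use were less common among adherent patients, the directions would swap.

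**The case against.** The strongest reply is that this is a condensed article. It says the listed variables will be considered, not that no others will be, and the Discussion speaks openly of possible confounders and predictive factors. A fuller document could add prior use. This lowers the weight of the point but does not remove it: the article spells its covariates out to the level of ATC and ICD codes and, where it turns to drug use, limits the item to other drugs.

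The second reply is that much of the difference is already adjusted for: hypertension, dyslipidaemia, diabetes, CHD, heart failure, the Charlson index, lipids, blood pressure, glycated haemoglobin, renal function and primary-care visits. This stands. Only a residual is in question.

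A third reply is that prior use of one drug group need not predict adherence to all four, which is what the adherent category requires. This also stands, and it makes the assumed prevalences loose. Objective 2 is also worded around sociodemographic and clinical features, so prior dispensing is not plainly within its scope.

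Stronger readings that a reader might infer are not supported:
- *Prior use is unobtainable.* SIDIAP holds the prescriptions and invoices; it is only not planned as a variable.
- *The HR is biased towards 1.* That follows only if prior users are both more adherent and at higher residual risk. The article supports neither.
- *The HR contrasts established with new users instead of adherent with nonadherent patients.* The groups are defined by post-index dispensing, so the planned contrast is made, possibly with confounding.
- *Table 3 shows that prior treatment is common.* Its title presents diseases of interest or grounds for exclusion; it gives no frequencies.
- *Stock left over at the index date must be credited.* The article explicitly defines adherence as six packages received in eight months. Changing that is a separate matter of exposure measurement.

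**Conclusion.** The point holds as a gap in a stated covariate set. Use of the four study groups before the ACS is not among the listed confounders and is not handled by eligibility, so prior users and new starters are pooled. The adjusted HR may therefore carry residual confounding beyond what the listed comorbidities and clinical parameters remove.

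The documents fix neither its size nor its direction. Under the assumptions shown, the bias factor is roughly 0.9 to 1.2 for most combinations and 0.87 to 1.31 at the corners. It is 1 if prior use is balanced between the groups or unrelated to residual risk. At the mild end the effect is negligible; at the far end it would change the reading of an HR near 0.72. The plan should be amended because the check is cheap, not because a bias has been demonstrated.

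**What to change.** - From the prescription and invoice data already in SIDIAP, extract dispensing of each of the four study groups in a fixed window before the index date, for example 6 to 12 months.
- Add prior use (yes/no per group, four binary variables) to the adjusted Cox models and to the objective 2 models.
- Report the main HR in patients with no prior use of any study group as a sensitivity analysis.
- State whether the other CVD drugs are measured before the index date or during follow-up.

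Leave the six-package adherence definition as it is.

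The cost is one more extraction from a source already in use and four covariates. The article does not say how far back the invoice data reach, so look-back may be short or missing for the earliest index dates; those patients should be flagged. The new-starter subgroup will be smaller than the expected 3400 or so, by an unknown amount, and its HR less precise. A yes/no variable also does not separate regular from irregular earlier refilling, so some confounding can remain.

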#### Patient Baseline Characteristics

All sociodemographic characteristics will be measured on the index date: index year, number of visits to PHC, age, sex, MEDEA index (socioeconomic deprivation index) [27], smoking status, alcohol intake, height, weight, Body Mass Index (BMI); the information comes primarily from a codified variable. If the patient has no information, it is calculated from height and weight and physical activity.

**Table 3 table3:** ICD-10 codes for comorbidities of interest or diseases for exclusion

ICD-10 code	Description
I24*, I25*	Coronary heart disease
I63*, I65*, I66*, I67.2, I67.8	Ischaemic stroke
G45	Transient cerebral ischaemic attack
I70*, I73*, I74*	Peripheral vascular disease
E78*	Dyslipidaemia
I10*, I15*	Hypertension
E10*, E11*	Diabetes mellitus
I48	Atrial fibrillation
I50*	Heart failure
C00*-C97*	Malignancies
J40*-J44*	Chronic obstructive pulmonary disease
F30*-F39*	Depression
M05*, M06*, M15*-M19*	Arthritis (osteoarthritis or rheumatoid arthritis)
M80*, M81*	Osteoporosis
N18*	Chronic kidney disease
B20*-B24*	HIV
G30*, G31*	Alzheimer’s disease, other dementias

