## Discussion

We expect to find that adherent patients have a lower risk of the primary endpoints in comparison with nonadherent patients.

Selection bias is a common limitation in observational studies. In order to avoid this bias, where the population with missing data differs from those with complete data, missing values for continuous variables will be imputed instead of excluding records with missing data.

Another limitation is the presence of potential confounders. To minimize confounders’ effects, Cox regression models adjusted for sociodemographic characteristics and for possible confounders and predictive factors will be used.

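### Concomitant drugs are called baseline but collected over all of follow-up, and clinical covariates have no before/after limit, so the adjusted adherence HR may use post-index information

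*Protocol article*

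**What the plan says.** All places are in the protocol article.

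- **Role of the covariates.** Other Variables: "All the following variables will be considered as potential confounders or effect modifiers" of the association between adherence and the composite endpoint. The Discussion gives the use: "Cox regression models adjusted for sociodemographic characteristics and for possible confounders and predictive factors will be used".
- **Concomitant drugs.** Concomitant Drug Use: "baseline information on other medications for CVD prescribed throughout follow-up will be captured from the pharmacy invoice".
- **Clinical parameters and comorbidities.** Comorbidities and Clinical Parameters: "They will be measured closest to the index date". The list covers lipids, blood pressure, glycated haemoglobin, renal function, coded comorbidities and a comorbidity index. It also includes "presence of coronary angioplasty implant after the event".
- **Contrast.** Patient Baseline Characteristics: "All sociodemographic characteristics will be measured on the index date".
- **Clock.** Study Population: "Index date definition: date of ACS episode". Under Primary Endpoint, follow-up runs from that date to the first component event or the end of follow-up. Under Adherence Definition, exposure is measured over the first eight months after it.
- **Model.** Statistical analysis names Cox regression with raw and adjusted HRs and multiple imputation of missing baseline values. It mentions no time-updated covariate.

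**The concern.** A confounder of the adherence effect should be fixed before adherence and outcome begin to unfold. As worded, the concomitant-drug variable runs alongside both. It can change after the eight-month adherence window has closed, and a long event-free follow-up gives more opportunity to be recorded as a user. Used as a fixed covariate, it would look protective whatever the drug does, and it would distort the adherence HR whenever adherent and nonadherent patients start such drugs at different rates.

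For lipids and blood pressure the risk is a different one. Statins, beta-blockers and ACEI/ARB act on these measures, so a value taken on treatment lies on the path from adherence to outcome. Adjusting for it removes part of the effect under study.

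Covariate adjustment is the only remedy for confounding that the article offers, so the meaning of the adjusted HR depends on these windows.

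**Working it through.** **1. The plan's own figures.** The plan gives no figure on covariate timing. Its one sample-size figure reproduces: 3415 cases / 3 years × 10 years × 0.30 = 3415, against a stated 3400 or so. Date limits on covariates leave it unchanged.

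**2. The windows side by side.**

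| Item | Window stated |
|---|---|
| Outcome clock | starts at the index date |
| Adherence | first 8 months after the index date |
| Sociodemographics | on the index date |
| Concomitant drugs | called baseline; covers all of follow-up |
| Clinical parameters, comorbidities | nearest to the index date; no direction, no maximum distance |
| Angioplasty | after the event, within the same nearest-to-index list |

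Inclusion starts in 2006 and follow-up goes to 2016. A baseline drug could therefore be first dispensed about 10 years after the index date (2016 − 2006).

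**3. Why a fixed user flag creates immortal time.** Suppose a drug is started at a constant rate s, unrelated to outcome. A patient followed for t years is flagged with probability 1 − exp(−s·t). With an assumed s of 0.15 per year:

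- t = 1: 1 − exp(−0.15) = 0.14
- t = 11: 1 − exp(−1.65) = 0.81

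The flag measures time survived event-free.

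**4. Illustrative simulation.** The documents supply none of the inputs, so all are assumptions:

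- 100,000 patients per scenario, with one pre-index confounder
- adherent share about 25% (45% in the last row), with adherence treated as known at time zero
- direct adherence HR 0.85
- a post-index marker lowered by 0 to 1 SD through adherence, with log-HR 0.25 per SD
- baseline event rate 0.08 per year and follow-up of 1 to 11 years
- an added drug with no effect on outcome, flagged if started before the event or censoring

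| Adherent share | Marker shift (SD) | Drug start per year, adherent / nonadherent | Adherence HR, pre-index adjustment | + post-index marker | + drug during follow-up | HR given to the null drug |
|---|---|---|---|---|---|---|
| 25% | 0.5 | 0.15 / 0.15 | 0.75 | 0.85 | 0.76 | 0.35 |
| 25% | 0.5 | 0.25 / 0.10 | 0.76 | 0.85 | 1.04 | 0.36 |
| 25% | 0.5 | 0.10 / 0.25 | 0.76 | 0.85 | 0.54 | 0.31 |
| 25% | 0.25 | 0.15 / 0.15 | 0.81 | 0.86 | 0.82 | 0.36 |
| 25% | 1.0 | 0.15 / 0.15 | 0.66 | 0.84 | 0.67 | 0.37 |
| 25% | 0 | 0.25 / 0.10 | 0.86 | 0.86 | 1.19 | 0.36 |
| 45% | 0.5 | 0.25 / 0.10 | 0.76 | 0.86 | 1.07 | 0.34 |

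The marker columns agree with the direct formula, total HR ≈ 0.85 × exp(−0.25 × shift). It gives 0.80, 0.75 and 0.66 for shifts of 0.25, 0.5 and 1 SD. Adjusting for the marker brings each back to about the direct 0.85.

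**5. Reading the table.** The null drug always looks strongly protective. The adherence HR hardly changes when start rates are equal. It moves in either direction when they differ. A marker that adherence does not shift does no harm.

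**The case against.** Several stronger readings are tempting, and the text does not carry them.

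- **That lipids and blood pressure are taken after the index date.** The wording permits this but does not require it. The nearest value may precede the event, and the plan to impute missing baseline values suggests a baseline intent. The defect is a missing limit. It still matters: SIDIAP laboratory data are primary-care tests, so a patient without a recent one before the event could be assigned a later, on-treatment value.
- **That the angioplasty variable counts later procedures.** It is listed next to the type of index event and under the nearest-to-index rule, and any treatment of the index episode necessarily follows it. The natural reading is the index procedure, a legitimate confounder. One clarifying phrase is enough.
- **That drugs started because of a recurrence enter the model.** Primary follow-up ends at the first component event, so such drugs are not clearly captured. Immortal time does not depend on this; stopping at the event is what leaves early failures little time to become users.
- **That the adjusted HR does condition on mediators and future events.** The variables are only candidates, and no covariate list is given. The final set may stand in a fuller document not shown.
- **That the bias can be sized from the cited HR of 0.72.** That HR comes from a two-drug cohort comparing at least 80% with under 40% of days covered. This study sets at least 75% on all four groups against everyone else. Any mediated share would also be assumed.

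The objection does not reach Concomitant Drug Use: its definition is written down, contradicts itself, and would pass into any analysis that follows it.

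**Conclusion.** The point holds in a limited form. The concomitant-drug definition contradicts itself. Following it in a Cox model with fixed covariates would put post-index information and immortal time into the adjusted HR. The rule for clinical parameters and comorbidities sets no before/after limit, so adjustment may use values that already reflect treatment.

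Neither the size nor the direction of the effect on the adherence HR can be derived from the document. The simulated range, from almost no change to 0.54 or 1.04 around 0.76 in the main scenarios, shows only that the problem can matter. It rests on the assumed inputs and on the drug entering as a fixed covariate. Confidence is high for the drug definition and lower for the clinical parameters, where the fault is an open window. The windows should be settled before extraction.

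**What to change.** 1. **Concomitant drugs.** Define the adjustment covariates from pharmacy invoices in a fixed window before the index date.
2. **Clinical parameters and comorbidities.** Use the last record on or before the index date within a fixed look-back. A measurement with no value there is missing and is imputed.
3. **Angioplasty.** State that it means the procedure during the index admission. This is the one permitted exception to the pre-index rule, since it follows the event by definition.
4. **Later co-medication.** Report it descriptively, or enter it only as a properly time-updated covariate.

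The cost is date filters at extraction; the number of patients does not change. There are two drawbacks. More baseline values will be missing, so the imputation must cover every affected variable: the Discussion speaks only of continuous ones, while Statistical analysis speaks of baseline values in general. Co-medication started at discharge, which may reflect the severity of the index event, will not be adjusted for; the report should say so.
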